#### Secondary and additional outcomes

Secondary and additional outcome analyses will involve contrasts comparing change on secondary (DQ-5, SCAS, ISI), and other (e.g., SIDAS) outcomes from baseline to other occasions of measurement, using an MMRM approach, as already described.

#### Additional analyses

Subsidiary complier analyses will be undertaken to compare individuals who complete the intervention relative to those who do not, in both trial stages. Regression models will be used to examine risk factors for symptoms of psychopathology across the study measurement points in the control arm. Mediation analyses will be explored using structural equation modelling. Machine learning approaches will be used to link multiple data types with outcomes to discover novel factors which predict outcomes in terms of specific disorders and their progression as well as investigate individual patterns of data that predict individual mental state or symptom trajectory. Cost-effectiveness analyses will be conducted at the primary endpoint and the final measurement point. Data will be linked to existing records, and education and health outcomes will be reported.

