#### Strategies to enhance and monitor adherence

To enhance adherence, digital notifications and reminders will be sent to participants reminding them to activate, visit and use the app/s as intended. Schools will provide class time to complete some of the activities contained in the apps (minimum of four class sessions), with the rest set for homework. School staff will provide verbal reminders and encouragement to students to use the Future Proofing App and, for intervention arm schools, the first intervention app (Stage I; SPARX) during the intervention implementation period. There will also be a $20 one-off incentive to cover any connectivity and data costs, delivered post intervention, to participants in both arms, which may serve to improve adherence. Adherence to the intervention app/s will be monitored by evaluating usage data that are collected automatically by the apps while they are active. Usage data are available at the individual level and consist of when and how many times users enter the apps, how long they spend in the app, how many modules they complete and, for Sleep Ninja only, any sleep tracking data that are input by the user.

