### Sample size

Separate sample size estimates were derived to determine the numbers of participants needed to meet the aims of each trial stage. Power was set at 0.80, α = 0.05 (two-tailed), and a correlation of 0.5 assumed between baseline and endpoint symptom scores. To account for possible clustering effects at Stage I (i.e., participants from the same school having prognostically relevant characteristics and outcomes more alike than between schools), a design effect [84] was calculated assuming an intraclass correlation coefficient (ICC) of 0.03 (based on previous school-based studies) [85] and a cluster size of 50 students, yielding a design effect of 2.47. In order to detect a mean standardized difference of 0.3 between conditions at Stage I, a sample of 870 participants would be needed (435 per arm). Allowing for up to 30% attrition, recruitment of 1244 participants would be required (622 per arm).

Using similar parameters for Stage II (without a design effect) would require recruitment of 368 participants in total to detect the same effect size. However, participants in this stage must meet eligibility requirements regarding elevated symptoms and failure to respond to the first-stage intervention. They must also be willing to participate. Accordingly, a scenario involving recruitment of 10,000 participants at Stage I was considered, assuming 7000 participants would have endpoint data available at 12 months (allowing for 30% attrition). Conservatively estimating 20% having PHQ-A scores ≥ 10, 25% showing a reduction due to the Stage I intervention and that 50% of those eligible to enrol at Stage II do so, 525 participants would enter this stage II, with endpoint data available for at least 368 (allowing for up to 30% attrition). This sample would enable the detection of differences in changes in symptomatology scores of comparable size to those in Stage I of the trial (*d* = 0.29).

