### Randomisation

For Stage I, cluster randomisation (at the school level) will be employed for administrative convenience, to avoid control condition contamination, and for the ecological validity of providing the intervention at the cluster level. Schools will be randomised after they are recruited into the trial. The trial statistician who is not involved in the day-to-day running of the trial will perform the randomisation, and the identity of the school will be concealed from the statistician.

Schools will be randomised with a 1:1 allocation, as per a computer-generated randomisation schedule. Balance between the trial arms will be achieved by stratifying based on school size, school location (metropolitan vs. regional), school type (co-educational or gender selective) and Index of Community Socio-Educational Advantage (ICSEA) level. For Stage II, individual-level randomisation with a 1:1 allocation using a computer-generated randomisation schedule stratified by gender and depression severity scores will be employed. This procedure is automated through the Black Dog Institute research platform. Permuted block randomisation will be used at both stages but will not be disclosed to ensure concealment. Allocation to arms is not directly communicated to schools. However, because the study has no control intervention, schools, participants and study operational staff will be aware of school allocation to the intervention arm. With the exception of the trial data manager, other individuals not involved in the day-to-day running of the trial will remain blind to allocation. All outcome assessments are conducted electronically and not subject to assessor bias. Unblinding at the conclusion of analysis will be performed by the trial data manager with authorisation from the Trial Steering Committee.

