### Analysis

#### Primary outcome

Analysis of the primary outcome will be undertaken using an intention-to-treat approach including all participants randomised regardless of intervention received, controlling for baseline differences when appropriate. The primary analysis will be conducted using planned contrasts comparing a change in depression scores on the PHQ-A from baseline to 12 months between the trial arms (SPARX intervention vs. control), using a mixed-effects model repeated-measure analysis (MMRM). MMRM is preferred due to the ability of this approach to include participants with missing data without using discredited techniques such as last observation carried forward [87, 88]. School will be included as a random effect to evaluate and accommodate clustering effects. Variables used in determining allocation balance will be evaluated and retained in analyses where they are significant or quasi-significant. An unconstrained variance–covariance matrix will model within-individual dependencies. Transformation of scores, including categorisation, may be undertaken to meet distributional assumptions and accommodate outliers.

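### The subsidiary complier analysis compares self-selected completers with non-completers, so it can show a benefit or a harm even if the app does nothing

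*Protocol article*

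**What the plan says.** The Additional analyses section of the protocol article defines the contrast in one sentence: "Subsidiary complier analyses will be undertaken to compare individuals who complete the intervention relative to those who do not, in both trial stages".

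Completion would come from the apps' own records. Strategies to enhance and monitor adherence says "Usage data are available at the individual level", and the items listed include "how long they spend in the app, how many modules they complete". The comparator has no app of its own to complete. The Randomisation section notes that "because the study has no control intervention, schools, participants and study operational staff will be aware of school allocation".

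The primary analysis is different in kind. It follows an "intention-to-treat approach including all participants randomised regardless of intervention received" and rests on "planned contrasts comparing a change in depression scores on the PHQ-A from baseline to 12 months between the trial arms". Secondary outcomes use the same change-from-baseline approach.

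**The concern.** Randomisation makes the arms comparable. It does not make finishers and non-finishers comparable, because finishing happens afterwards and depends on the student and the school.

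The protocol's own delivery plan leaves room for this selection:

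- SPARX has seven modules of about 20 minutes. Schools must give four 20-minute class sessions and may give up to seven (Procedure and participant timeline). At the minimum, three modules fall to the student's own time, and the amount of support varies by school.
- Sleep Ninja has six levels. Each needs a training session and three nights of tracking within one week, all in the student's own time over six weeks. There is almost no slack.

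Motivation, symptom level, personality and school support can all affect finishing, and can also affect later depression scores. The completer contrast then estimates a mixture of selection and effect. Ethics and dissemination says findings will go to schools, parents and government policy documents. A favourable completer result would easily be read there as proof that the app works when used, and an unfavourable one as proof of harm. The contrast supports neither reading.

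**Working it through.** **Inputs from the protocol (Sample size section).** "Power was set at 0.80, α = 0.05 (two-tailed), and a correlation of 0.5 assumed between baseline and endpoint symptom scores"; "assuming an intraclass correlation coefficient (ICC) of 0.03"; cluster size 50; planning effect 0.3 SD; 7000 participants with 12-month data if 10,000 are recruited. Allocation is 1:1, so about 3500 of the 7000 are in the intervention arm.

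**The plan's own figure first.** Design effect = 1 + (50 − 1) × 0.03 = 2.47. With correlation 0.5, the change-score SD is √(2 × (1 − 0.5)) = 1 in units of the raw SD. The t-based sample size for 0.3 SD is 176 per arm; 176 × 2.47 = 434.7, so 435 per arm and 870 in total. Then 435 / 0.7 = 621.4, so 622 per arm and 1244 in total. These figures reproduce, and this point does not touch them.

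**Assumptions (not in the document).** Completion of 20%, 40% or 60%; selection strength of 0.5 on the log-odds scale per SD; an unmeasured prognostic factor *u* correlated 0.3 with the 12-month score.

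**Model with no app effect.** Baseline *b* and *u* are independent standard normals, and 12-month score *y* = 0.5*b* + 0.3*u* + error, scaled to SD 1. Completers are the stated fraction with the highest propensity, which depends on *b*, on *u*, or on both. There were 1,000,000 simulated intervention-arm students per scenario. Negative values mean that completers look better.

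| Who completes | Gap in 12-month score | Gap in change | Gap adjusted for baseline | Chance of p < 0.05 on change |
|---|---|---|---|---|
| Unrelated to prognosis | 0.00 | 0.00 | 0.00 | 5% |
| Low baseline scores | −0.24 | +0.24 | 0.00 | 95–99% |
| High baseline scores | +0.24 | −0.24 | 0.00 | 94–99% |
| Good unmeasured prognosis | about −0.14 | about −0.14 | about −0.14 | 60–74% |
| Poor unmeasured prognosis | about +0.14 | about +0.14 | about +0.14 | 60–77% |
| Low baseline (strength 0.3) and good unmeasured prognosis (0.5) | about −0.28 | 0.00 | about −0.14 | 5% |

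Ranges cover the three completion rates.

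**Why the signs differ.** If low-baseline students complete, the baseline gap is about −0.47 SD. The 12-month gap is 0.5 × (−0.47) = −0.24, so the gap in change is −0.24 − (−0.47) = about +0.24, which is regression to the mean. If selection is on *u*, the gap in *u* is also about 0.47 SD, and 0.3 × 0.47 = 0.14. Baseline adjustment cannot remove that part.

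**Rejection rates.** SE = √(2.47 × [1/(3500p) + 1/(3500(1 − p))]), where p is the completion rate: 0.066 at 20% and 0.054 at 40% or 60%. At 40%, 0.141 / 0.054 = 2.6, which gives 74% rejection. These rates are for Stage I in the 10,000-recruit scenario. No rate was computed for Stage II, where the same mechanism applies.

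**The case against.** **It is one sentence in a condensed article, and complier analysis is also the usual name for a complier-effect estimate.** The completion threshold, covariates and model may well sit in the analysis plan, and their absence here is not a fault. But the sentence does state which groups are compared, and they are completers and non-completers. If a complier average causal effect was meant, label and description disagree. Reading the non-completers as including controls does not help, because self-selected completers would still face a group that randomisation did not create.

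**Baseline adjustment and the school random effect would deal with some of the selection.** This stands in part. In the scenarios driven only by baseline score, adjustment takes the bias to zero. It leaves about 0.14 SD from the unmeasured factor.

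**The analysis is subsidiary, and no hypothesis concerns completers.** This stands, and it limits the severity.

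**A reader might infer that the contrast is bound to favour the app.** If only students with better 12-month scores finish, the unadjusted 12-month gap at an assumed 50% completion is 2 × 0.798 × |r|, or 0.16, 0.32 and 0.48 SD for |r| = 0.1, 0.2 and 0.3. That result builds the direction in and uses the raw score. The protocol's contrasts are of change from baseline, on which the bias can be a benefit, a harm or nothing. The document says nothing about who will complete.

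**The instrumental-variable alternative has its own assumptions.** This also stands. Dividing the intention-to-treat effect by the completion rate requires no effect below the completion threshold, which is doubtful for seven modules teaching separate skills. Suppose (assumed figures) 40% complete and gain 0.30 SD, and another 40% use the app partly and gain 0.15 SD. The intention-to-treat effect is 0.4 × 0.30 + 0.4 × 0.15 = 0.18 SD, and 0.18 / 0.40 = 0.45 SD overstates the completers' 0.30 by half. With any use as the threshold, 0.18 / 0.80 = 0.225 SD, the true average among users. Absence of app use in controls also has to be checked, particularly at Stage II, where individuals are randomised.

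**Conclusion.** The point holds: as worded, the completer contrast is not protected by randomisation and can show a difference when the app does nothing. Under the assumed single-factor selection, the false difference in change is about 0.14 to 0.24 SD in either direction. That is about half (0.14 / 0.30 = 0.47) to four fifths (0.24 / 0.30 = 0.80) of the 0.3 SD planning effect. About 0.14 SD from an unmeasured factor survives baseline adjustment. With some 3500 intervention-arm students, false differences of this size would often reach significance. All sizes depend on assumed completion rates and selection strengths. With no selection the bias is zero, and with mixed selection it can cancel on the change score.

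A reader might go further and conclude that the trial's main result is compromised. The documents do not support that, because the primary comparison is by randomised arm and does not use completion. The change is worth making but concerns a subsidiary analysis only.

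**What to change.** Replace the sentence under Additional analyses so that, for each stage:

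- The effect of completion is estimated as a complier average causal effect, with randomised allocation as instrument and completion recorded in the usage data as exposure.
- The model adjusts for baseline PHQ-A (at Stage II, the score at entry to that stage) and that stage's stratification factors, and respects school clustering at Stage I.
- The exclusion restriction is stated: allocation has no effect on those below the completion threshold. The analysis is repeated with a lower threshold such as any use, because partial users may benefit.
- Usage data are used to confirm that controls had no access to the app under test.
- Differences between completers and non-completers are reported only as descriptive and non-causal.

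The cost is a wording change and one instrumental-variable model per stage, repeated at the lower threshold, using data already collected. The interval is wider. Ignoring sampling error in the completion rate, it is about 1 / 0.4 = 2.5 times the intention-to-treat interval at an assumed 40% completion. The estimate essentially rescales the intention-to-treat effect, so it adds no independent evidence that the app works, and it is only as sound as the stated assumptions.

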#### Interim analyses

The percentage of participants meeting PHQ-A depression caseness, scores and reporting of suicidality at each assessment within both groups will be measured and reviewed by the DSMC in order to monitor relative levels of deterioration (accounting for baseline levels), for safety purposes.

### Ethics and dissemination

This study has ethical approval from the University of New South Wales Human Research Ethics Committee (HC180836) and NSW Government State Education Research Applications Process Approval (SERAP 2019201), and has applied for approval from Catholic dioceses and the Tasmanian Department of Education. The trial is subject to annual progress reviews with these ethics bodies. The trial is registered with the Australian New Zealand Clinical Trials Registry (ANZCTRN12619000855123). All protocol amendments will be subject to approval by relevant ethics committees and listed on the ANZCTR registry. All trial findings will be presented in aggregate format so that no individual-level data will be presented.

Public access to the full protocol can be granted from the authors on reasonable request. Access to participant-level dataset will be subject to governance processes set up around a data repository which will contain data from this study. This will be open for researchers to apply for access.

Trial findings will be communicated using lay language and will be made available to participating schools for publication in school newsletters and/or school websites. Participants and parents will also be provided with these findings via email. Regular trial progress updates will be provided by the research team to schools for distribution through the school community, at their discretion. These findings will also be provided to other stakeholders in the wider community, including to the government in policy documents, school counsellor bodies, teacher groups and mental health groups. All findings will be provided at aggregate level. The results of the trial will be disseminated via peer-reviewed publications in scientific journals and conferences. No restrictions have been imposed on the dissemination of information by funders.

## Discussion

The prevention of depression is critical if the burden of disease is to be reduced. This study will be the first to examine the prevention of depression in young people at scale, using easy-to-access, convenient and private mobile-phone applications. Efficacy of depression prevention has been established [17, 19]. What The Future Proofing Study provides is a large definitive trial investigating the impact of delivering evidence-based prevention programmes like CBT at scale, in real-world settings. A large-scale trial such as this can provide insight into scaling and implementation processes, which can form the basis of an ongoing delivery and dissemination framework. The current study meets this need by examining a depression-prevention programme, delivered by mobile phone applications, with access facilitated in the school environment that is where young people spend most of their time. This means that, if successful, schools could become the setting in which access to these programmes is rolled out continually, future proofing and inoculating all young people who go through the school system against mental illness.

There are several other features of this trial that make it novel. The use of a two-staged design, such that those who show symptoms of depression at the primary endpoint are randomised to receive a second intervention targeting insomnia, is innovative. This second intervention offers an alternative way to reduce risk for depression onset. The use of smartphone apps as the primary intervention delivery mechanism is new in this area [27, 89] and promises reduced costs and access barriers compared to traditional face-to-face and health professional-led programmes. The inclusion of smartphone-collected objective data adds another dimension to the trial, allowing for machine learning approaches to explore whether activity and location data are associated with, or predictive of, changes in depression and other mental health symptoms. Moreover, linking this rich dataset to government education and health records will permit direct inferences to be made about the impact of mental illness on health and academic outcomes. Finally, the continuation of follow-up assessments for 5 years means that the long-term effects of the interventions on depression, anxiety, distress, insomnia and additional outcomes can be assessed. The results of The Future Proofing Study stand to provide a major contribution to the field of digital mental health prevention programmes, and knowledge about the population-level impact of preventing depression using these methods.

## Data Availability

Not applicable.

## Abbreviations

CBT: Cognitive behaviour therapy
CBT-I: Cognitive behaviour therapy for insomnia
RCT: Randomised controlled trial
